### 6.4. Documentation of Stop Criteria/Study Dropout

Reason for dropout;Time Point of dropout;UTI;Sepsis;Adverse events;Problems of administration of the drug;Duration of non-antibiotic regimen;Switch to another prophylaxis regimen/which one.

### 6.5. Blinding of Study Assessors

Study assessors will not be blinded.

## 7. Statistical Considerations

Power analysis was performed to determine an adequate sample size. We considered that these patients suffer 9.4 UTIs per year with an SD of 5.414. Furthermore, we assumed that a reduction of 3 UTIs per year is clinically significant. In order to achieve an effect size of 0.1, 785 participants are necessary (power = 0.87; alpha = 0.05). Furthermore, to achieve an effect size of 0.2, 197 participants are necessary, or for an effect size of 0.3, 88 participants are required, respectively. Data measured on a continuous scale will be expressed as mean, standard deviation, range, and median. Counts and percentages of patients in the categories will be used to convey categorical data. When necessary, T- or Mann-Whitney tests will be performed to determine statistical differences in continuous variables, and Chi-square or Fisher’s tests will be used to test for statistical differences in categorical variables.

Patients with a minimum follow-up of 6 months who remained on the same prophylaxis regimen will be eligible for the final statistical analysis. 

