## Abstract

Introduction: Patients with neurogenic lower urinary tract dysfunction (NLUTD) reliant on intermittent self-catheterization for bladder emptying are at an increased risk of recurrent urinary tract infections (rUTI). So far, the most common practice in the prevention of rUTIs is long-term low-dose antibiotic prophylaxis, phytotherapy, and immunomodulation, whereby antibiotic prophylaxis inevitably leads to the emergence of drug-resistant pathogens and difficulty in treating infections. Therefore, non-antibiotic alternatives in the prevention of rUTIs are urgently required. We aim to identify the comparative clinical effectiveness of a non-antibiotic prophylaxis regimen in the prevention of recurrent urinary tract infections in patients with neurogenic bladder dysfunction who practice intermittent self-catheterization. Methods and analysis: In this multi-centre, prospective longitudinal multi-arm observational study, a total of 785 patients practising intermittent self-catheterisation due to NLUTD will be included. After inclusion, non-antibiotic prophylaxis regimens will be instilled with either UroVaxom^®^ (OM-89) standard regimen, StroVac^®^ (bacterial lysate vaccine) standard regimen, Angocin^®^, D-mannose (oral dose 2 g), bladder irrigation with saline (once per day). The management protocols will be pre-defined, but the selection of the protocol will be at the clinicians’ discretion. Patients will be followed for 12 months from the onset of the prophylaxis protocol. The primary outcome is to identify the incidence of breakthrough infections. The secondary outcomes are adverse events associated with the prophylaxis regimens and the severity of breakthrough infections. Other outcomes include the exploration of change in susceptibility pattern via the optional rectal and perineal swab, as well as health-related quality of life over time (HRQoL), which will be measured in a random subgroup of 30 patients. Ethics and dissemination: Ethical approval for this study has been granted by the ethical review board of the University Medical Centre Rostock (A 2021-0238 from 28 October 2021). The results will be published in a peer-reviewed journal and presented at relevant meetings. Study registration number: German Clinical Trials Register: Number DRKS00029142.

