## 2. Objectives

The aim of this prospective observational cohort study is to investigate the impact of five different non-antibiotic prophylaxis regimens over the course of one year on predefined time points. Our long-term goal is to identify safe and effective candidate regimens that could be carried to a randomised controlled trial (RCT) to establish clinical and cost-effectiveness. 

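### The 785 total does not follow from the stated 3-UTI target, and at two-sided 5% its formula gives 80% power, not the printed 87%

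*Protocol article*

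**What the plan says.** Section 7 (Statistical Considerations) starts from clinical inputs: "We considered that these patients suffer 9.4 UTIs per year with an SD of 5.414", and "we assumed that a reduction of 3 UTIs per year is clinically significant". It then moves to a different scale: "In order to achieve an effect size of 0.1, 785 participants are necessary", with power 0.87 and alpha 0.05 in brackets. Two alternatives follow: "to achieve an effect size of 0.2, 197 participants are necessary, or for an effect size of 0.3, 88 participants are required". The section does not name the effect-size metric, the test behind the calculation or whether it is one- or two-sided.

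The Abstract adopts the first figure: "a total of 785 patients practising intermittent self-catheterisation due to NLUTD will be included". Section 2 sets the aim to "investigate the impact of five different non-antibiotic prophylaxis regimens over the course of one year". On allocation, the Abstract says "The management protocols will be pre-defined, but the selection of the protocol will be at the" discretion of the clinicians. Section 7 names t or Mann-Whitney tests for continuous variables. It restricts the final analysis to patients followed for at least 6 months who stayed on one regimen.

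**The concern.** The paragraph sets out a mean, an SD and a clinically meaningful change, which is what a sample size for a UTI rate needs, and then does not use them. None of 0.1, 0.2 and 0.3 is the standardised form of 3 UTIs per year. The printed power also does not match the printed totals under the usual two-sided convention.

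The sample size is the main quantitative justification for the study, and a reader cannot tell what 785 was meant to detect. If two regimens do not differ at the end, it will be unclear whether the plan aimed to exclude a difference of 3 UTIs per year or one of about half a UTI. Section 2 says the results are to pick candidate regimens for a later randomised trial, so that distinction matters.

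**Working it through.** **Inputs, all from Section 7 unless noted.** Rate 9.4 UTIs per year; SD 5.414; target reduction 3; effect sizes 0.1, 0.2 and 0.3 with totals 785, 197 and 88; power 0.87; alpha 0.05. Five regimens (Section 2). Even arms of 785/5 = 157 are my assumption, since no split is given.

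**1. Reproducing the printed totals.** Take N = ((z_alpha + z_power)/ES)², rounded up.

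| Setting | Sum of z values | ES 0.1 | ES 0.2 | ES 0.3 |
|---|---|---|---|---|
| Printed (power 0.87) | – | 785 | 197 | 88 |
| Two-sided 0.05, power 0.80 | 1.960 + 0.842 | 785 | 197 | 88 |
| Two-sided 0.05, power 0.87 | 1.960 + 1.126 | 953 | 239 | 106 |
| One-sided 0.05, power 0.87 | 1.645 + 1.126 | 768 | 192 | 86 |

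Only the second row of settings, two-sided at 0.80, matches all three totals exactly (unrounded 784.9, 196.2 and 87.2). One-sided power at N = 785 is Φ(0.1 × √785 − 1.645) = Φ(1.157) = 0.876, close to the printed 0.87.

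The formula is that of a one-sample or paired mean and of a one-degree-of-freedom chi-square. It is also the normal-approximation total for two groups with the effect expressed as Cohen's f. The document does not say which was used.

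**2. The effect size implied by the clinical inputs.**
- d = 3/5.414 = 0.554.
- As a two-group f: 0.554/2 = 0.277.
- In reverse, 0.1 SD = 0.1 × 5.414 = 0.54 UTIs per year, which is 18% of the target of 3 (0.5414/3).

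**3. What 785 gives for a comparison of regimens at an effect size of 0.1.**
- Five-group ANOVA, f = 0.1, N = 785: power 0.59. About 1,419 in total would be needed for 0.87.
- Pairwise two-sided t-test, d = 0.1, 157 per arm: power 0.14.

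**4. What 785 gives for the stated target.** Two-sided t-test between two regimens, alpha 0.05, SD 5.414, difference 3:
- Needed per regimen: 53 for power 0.80 (unrounded 52.1) and 64 for 0.87 (unrounded 63.02).
- Five even arms at 64: 5 × 64 = 320 analysable patients.
- Power at 157 per arm: 99.8%.
- Detectable difference at 157 per arm and 80% power: about 0.32 SD, or 1.7 UTIs per year.

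**5. If the reduction is before-after within a regimen.** Taking 5.414 as the SD of the change (an assumption), the formula in step 1 with ES = 0.554 gives 26 per regimen at power 0.80 and 32 at 0.87. Neither contrast leads to 785.

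**The case against.** The strongest reply is that 785 is ample for the clinical target, so nothing is lost. The power part stands: at 157 per arm the power for 3 UTIs is close to 100%. A reader might infer from the 0.1 that the study is badly underpowered. The document does not support that, because it nowhere states 0.1 SD between two regimens as its goal.

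A second reply is that 0.1 may be on another scale. This also stands in part. A reader might conclude that a chi-square index was used, which would not suit a UTI count, but the same formula also serves a one-sample mean or a two-group f, so that cannot be asserted. On the f scale the target of 0.277 lies between the listed 0.2 and 0.3. Even so, no reading turns 3/5.414 into 0.1.

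Third, the test may have been one-sided, which would explain 0.87. It would not explain why all three totals match two-sided 0.80 exactly, and one-sidedness is not stated.

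Fourth, the article is condensed. That covers the absence of per-arm numbers, of a multiplicity rule and of a minimum arm size, which the full protocol or the analysis plan may settle; I do not count these as faults. It does not cover printed inputs that disagree with the printed effect size. Lastly, a reduction of 3 may mean before-after and not between regimens. The text allows both, so the contrast has to be named.

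**Conclusion.** The point holds as a fault in the justification. The effect size behind 785 does not follow from the stated SD and clinical target (0.1 against 0.554 SD, or 0.277 as a two-group f). Under a two-sided test, the printed power of 0.87 should read 0.80 for the printed totals. The formula used is not one for comparing five regimens.

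No shortage of patients is shown for the 3-UTI target. That conclusion rests on a between-regimen contrast, a common SD of 5.414, a two-sided test at 0.05 and reasonably even arms. The last condition is not secured, because clinicians choose the regimen and the 6-month same-regimen rule reduces the numbers analysed. Any regimen with fewer than about 64 analysable patients would fall below 87% power against another of the same size.

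**What to change.** Keep 785. In Section 7, replace the lines on effect sizes 0.1, 0.2 and 0.3 with one calculation on the primary outcome that:

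- names the contrast (between regimens, or before-after within a regimen), the test, the sidedness and alpha;
- uses the 3-UTI target and the SD of 5.414, saying what that SD refers to;
- gives a power figure that agrees with the number of patients;
- states what 785 detects. For a two-sided between-regimen t-test at 0.05 with even arms of 157, that is 99.8% power for 3 UTIs and a detectable difference of about 1.7 UTIs per year at 80% power;
- gives the analysable number per regimen this requires (64 for 87% power, 53 for 80%), counted in the 6-month same-regimen analysis set, and says that regimens below it will have less power than stated.

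A multiplicity adjustment is optional; if one is chosen, the per-regimen number should be recalculated with it.

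The cost is one rewritten paragraph and no extra patients. The downside is that the stated power becomes openly conditional on arm sizes that depend on clinicians' choices.

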### 4.2. Exclusion Criteria

Patients practising ISC with augmented bladder or continent pouches;Inability to consent;Intention-to-treat analysis for dropouts;Failure to provide consent;MDR pathogens in previous episodes of UTIs;Antibiotic prophylaxis in the months before study enrolment.

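### 785 is both the number enrolled and the uninflated number required, but Section 7 then removes early leavers and switchers, in conflict with Section 4.2, so the stated power is not delivered (minor)

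*Protocol article*

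**What the plan says.** The abstract sets the enrolment: "a total of 785 patients practising intermittent self-catheterisation due to NLUTD will be included". Section 7 gives the same figure as the requirement: "In order to achieve an effect size of 0.1, 785 participants are necessary (power = 0.87; alpha = 0.05". It adds two further sizes from the same calculation: "to achieve an effect size of 0.2, 197 participants are necessary, or for an effect size of 0.3, 88 participants are required, respectively". Its inputs are a yearly rate and spread ("We considered that these patients suffer 9.4 UTIs per year with an SD of 5.414") and a threshold of relevance ("we assumed that a reduction of 3 UTIs per year is clinically significant").

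The closing sentence of Section 7 defines who is analysed: "Patients with a minimum follow-up of 6 months who remained on the same prophylaxis regimen will be eligible for the final statistical analysis". Section 6.4 lists what is recorded when a patient stops, including "Switch to another prophylaxis regimen/which one". Section 4.2 has, as one of its exclusion criteria, the entry "Intention-to-treat analysis for dropouts".

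**The concern.** A number needed for a given power is a number analysed. Here that number is also the number enrolled, and a rule in the same section subtracts from it. The enrolment total, the requirement, the power and the analysis set agree only if no patient leaves before 6 months and none changes regimen. Section 6.4 shows that the authors foresee both, although it gives no rate.

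The entry in Section 4.2 adds a contradiction. It is not a criterion by which a patient could be excluded, and on its natural meaning it keeps patients whom Section 7 removes. A reader cannot tell which population the power statement describes. At stake is whether the figure printed in the article is the one that the study can deliver.

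**Working it through.** **Inputs.** From the documents: 785 enrolled (abstract); 785, 197 and 88 for effect sizes 0.1, 0.2 and 0.3, power 0.87, alpha 0.05, SD 5.414, difference of 3 UTIs per year (Section 7); five regimens (Section 3). Sidedness and type of effect size are not stated. The loss rates of 10%, 20% and 30% are assumptions, because the article gives none.

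**1. Reproduce 785.** One-sample (or paired) normal approximation, n = ((z_alpha + z_power)/d)^2, with two-sided alpha 0.05 and 80% power:

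- d = 0.1: (2.8016/0.1)^2 = 784.9, rounded up to 785
- d = 0.2: 196.2, rounded up to 197
- d = 0.3: 87.2, rounded up to 88

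All three match exactly, so none of them includes a loss factor.

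**2. Where 0.87 could come from.** With 785 and d = 0.1, d x sqrt(n) = 2.80. Two-sided power is Phi(2.80 - 1.96) = 0.80. One-sided power is Phi(2.80 - 1.645) = 0.876, the nearest to the stated 0.87. Two-sided power of 0.87 would need ((1.96 + 1.126)/0.1)^2, which rounds up to 953.

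**3. Apply the Section 7 restriction.** n = 785 x (1 - loss). Power = Phi(0.1 x sqrt(n) - z), with z = 1.96 or 1.645. Detectable effect at 80% two-sided power = 2.8016/sqrt(n); multiplied by 5.414 it is in UTIs per year.

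| Assumed loss | Analysed | Power, two-sided | Power, one-sided | Detectable effect (SD) | UTIs per year |
|---|---|---|---|---|---|
| 0% | 785 | 0.80 | 0.876 | 0.100 | 0.54 |
| 10% | 706 | 0.76 | 0.84 | 0.105 | 0.57 |
| 20% | 628 | 0.71 | 0.81 | 0.112 | 0.61 |
| 30% | 550 | 0.65 | 0.76 | 0.120 | 0.65 |

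On the one-sided reading, power of 0.87 needs ((1.645 + 1.126)/0.1)^2, which rounds up to 768. The margin is therefore 1 - 768/785, about 2%.

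**4. Does it matter for the stated 3-UTI difference?** 3/5.414 = 0.554 SD. Assume five equal arms, 785/5 = 157 each, and a two-sided comparison of two arms: power = Phi(3/(5.414 x sqrt(2/m)) - 1.96).

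- No loss, m = 157: Phi(4.91 - 1.96) = 0.998
- 30% loss, m = 110: Phi(4.11 - 1.96) = 0.98
- 30% loss, alpha 0.005 (ten pairwise comparisons): Phi(4.11 - 2.81) = 0.90

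**The case against.** The best defence has three parts.

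**An article may leave a dropout allowance to the full protocol.** This stands as far as it goes: the bare absence of a loss rate or replacement rule is no finding. What remains is that the article itself prints the enrolment, the requirement and the restriction, and these do not fit together.

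**Section 4.2 may govern.** If dropouts are analysed by intention to treat, switchers stay in and only true loss to follow-up reduces the number. That would shrink the shortfall. But Section 7 explicitly defines the final analysis set, and the Section 4.2 entry is misplaced, so the text does not settle the matter. Nor does Section 7 say whether a switch after month 6 also removes a patient.

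**The shift is small against what the authors call relevant.** This stands. At 30% loss the detectable effect moves by about 0.11 UTI per year, against a threshold of 3. The reservation is that equal arms are assumed in that check, while the abstract leaves the choice of regimen to the clinician.

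A reader might go further and infer that attrition is what would make a null comparison between regimens look better powered than it is. The documents do not support that. The 785 reproduces only on a one-sample basis. For d = 0.1 between two arms of 157, two-sided power is about 0.14 before any loss. The mismatch between the calculation and a five-regimen comparison is a separate issue, and attrition adds little to it.

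**Conclusion.** The point holds as a minor one. The stated requirement equals the enrolment, has no loss factor, and is followed by a rule that reduces the number analysed. At effect size 0.1, the stated power is not delivered at any realistic loss, and Sections 4.2 and 7 disagree on whether dropouts and switchers are analysed.

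The size depends on the assumed loss and on sidedness. At 10% to 30% loss, power is 0.76 to 0.65 two-sided, or 0.84 to 0.76 one-sided. It would be tempting to take 0.87 as the two-sided power at 785 and scale it down. That starting point is not available, because it implies a noncentrality of 3.086 where 785 gives 2.80.

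This does not threaten the study's ability to see a 3-UTI difference, provided that the arms are of similar size. It is a figure that is wrong as written and a contradiction that needs settling.

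**What to change.** Keep enrolment at 785 and change the text:

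1. In Section 7, say that 785 is the number enrolled, give the loss assumed from dropout and switching, and restate the power or the detectable effect for the number analysed, with the sidedness named.
2. Reconcile Section 7 with Section 4.2. Take the intention-to-treat entry out of the exclusion criteria, make analysis of all enrolled patients by the regimen started the primary analysis, and keep the Section 7 restricted set as a sensitivity analysis. State whether a switch after month 6 removes a patient from that set.

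The cost is a slightly less favourable stated figure and a little more analysis work. No extra patients are needed.

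### The stated power of 0.87 does not follow from 785, 197 and 88 participants: these are the 80%-power sizes for a two-sided, one-degree-of-freedom test, and not a calculation for five regimens

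*Protocol article*

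**What the plan says.** Section 7 (Statistical Considerations) first gives its clinical inputs: "We considered that these patients suffer 9.4 UTIs per year with an SD of 5.414", and "we assumed that a reduction of 3 UTIs per year is clinically significant". It then gives sample sizes for three effect sizes that it does not derive from those inputs: "In order to achieve an effect size of 0.1, 785 participants are necessary (power = 0.87; alpha = 0.05", followed by "to achieve an effect size of 0.2, 197 participants are necessary, or for an effect size of 0.3, 88 participants are required". The power and alpha are printed beside the first pair only; I take them to apply to all three.

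The section does not say which test was powered, which effect-size index is meant (w, f or d), how many degrees of freedom it has, or whether alpha is one- or two-sided. The tests it lists for analysis are t, Mann-Whitney, chi-square and Fisher, and none is called one-sided.

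The aim in Section 2 is to "investigate the impact of five different non-antibiotic prophylaxis regimens over the course of one year". The Abstract gives 785 as the total to be included and leaves the choice of regimen to the clinician. Section 7 ends by limiting the final analysis to patients with at least 6 months of follow-up who stayed on the same regimen.

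**The concern.** A power, an alpha, an effect size and a sample size are tied together by arithmetic, so a reader can check whether they agree. Here they do not under the usual two-sided alpha. The calculation is the only justification given for 785 patients. A reader would take from it a 13% risk of missing an effect of 0.1, when the sizes printed carry a 20% risk for a two-sided 1-df test.

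There is also a question of what was powered. The study compares five regimens, and an overall comparison of five groups has four degrees of freedom, but the numbers match a single-degree-of-freedom test. Finally, 785 is both the number to be included and the number needed, although Section 7 then removes some patients from the analysis.

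**Working it through.** **Inputs.** From Section 7: effect sizes 0.1, 0.2, 0.3; N = 785, 197, 88; alpha 0.05; power 0.87; SD 5.414; difference 3. From Section 2: five regimens. My assumptions: equal arms (785/5 = 157), and a 20% loss where stated.

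**1. Which power gives the printed sizes?** For a 1-df test with effect size w, the noncentrality is N·w². For two-sided alpha 0.05 and 80% power it must reach about (1.960 + 0.8416)² = 7.849.

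- w = 0.1: 7.849/0.01 = 784.9, so 785
- w = 0.2: 7.849/0.04 = 196.2, so 197
- w = 0.3: 7.849/0.09 = 87.2, so 88

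All three match exactly. Power at these N (noncentral chi-square) is 0.800, 0.802 and 0.804. With one patient fewer it is 0.7996, 0.7996 and 0.7991, so each is the smallest N that reaches 0.80.

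**2. What would 0.87 need, two-sided?** (1.960 + 1.1264)² = 9.526. Dividing by 0.01, 0.04 and 0.09 and rounding up gives 953, 239 and 106.

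**3. Can a one-sided test explain 0.87?** Power = Φ(w·√N − 1.645).

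- N = 785: Φ(2.802 − 1.645) = 0.876
- N = 197: Φ(2.807 − 1.645) = 0.877
- N = 88: Φ(2.814 − 1.645) = 0.879

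This is close, but each value rounds to 0.88. A one-sided target of 0.87 requires (1.645 + 1.1264)² = 7.680, hence 768, 192 and 86. None of these is the printed N.

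**4. Five regimens at the same abstract effect sizes.**

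| Effect size | N | Power, 4-df chi-square (w) | Power, five-group ANOVA (f) | N for 80% (chi-square) | N for 87% (chi-square) |
|---|---|---|---|---|---|
| 0.1 | 785 | 0.595 | 0.592 | 1194 | 1414 |
| 0.2 | 197 | 0.597 | 0.585 | 299 | 354 |
| 0.3 | 88 | 0.600 | 0.572 | 133 | 158 |

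**5. Five regimens at the article's own difference.** d = 3/5.414 = 0.554. With 157 per arm:

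- One pairwise comparison: d·√(157/2) = 4.91, and power = Φ(4.91 − 1.96) = 0.998. With Bonferroni over 10 pairs it is 0.98.
- Five-arm ANOVA, one arm differing by 3 from the other four: f = 0.554·√(0.2 × 0.8) = 0.222, power above 0.999.
- Five-arm ANOVA, two arms 3 apart and the other three midway: f = 0.554·√(0.5/5) = 0.175, power 0.986.

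**6. After exclusions.** With an assumed 20% loss, 785 × 0.8 = 628 remain. At effect 0.1, power is 0.71 (1 df) or 0.49 (4 df). At the 3-UTI difference the two ANOVA patterns give 0.998 and 0.956.

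**The case against.** The strongest reply is that the article never states sidedness. Its wording speaks of a reduction in UTIs, which could mean a before-after change in a single group. A one-degree-of-freedom test, even a one-sided one, would be natural for that, and it gives 0.876. A paired or one-sample test by normal approximation also yields 785, 197 and 88, so the chi-square test is not the only candidate. This stands in part: the index and test cannot be identified, and 0.87 cannot be called impossible. But the one-sided sizes for 0.87 would be 768, 192 and 86, whereas the two-sided 80% sizes match three times out of three. Nor would a before-after test be a calculation for comparing regimens.

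The second reply concerns the five-arm figure. A reader might infer from about 60% power that the study has a 40% chance of missing a difference that matters. The documents do not support that. The 60% depends on an effect of 0.1, 0.2 or 0.3 read as w or f at the matching N, and on a 4-df test that the article does not name. None of those effect sizes is derived from the difference the authors call clinically significant. At that difference, 785 patients are ample under equal arms. This reply stands.

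The 20% loss is my assumption, and attrition is a separate matter from the misstated power. It belongs here only because the corrected figure should be quoted at the number analysed.

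**Conclusion.** The power figure and the sample sizes in Section 7 disagree. Under two-sided alpha 0.05 with one degree of freedom, 785, 197 and 88 deliver 0.80, about 7 percentage points below the 0.87 printed. An undeclared one-sided test comes close but matches neither the power to two decimals nor the sizes. Neither reading addresses the five-regimen comparison, for which power at the same abstract effect sizes is 0.57 to 0.60.

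The conclusion stops there. It is an error in the stated justification, not evidence that the study is underpowered for a 3-UTI difference. For that difference, power is about 0.998 for one pairwise comparison and about 0.99 or higher for a five-arm ANOVA, on the two patterns of means tried. These last figures assume equal arms, which the protocol cannot guarantee because clinicians choose the regimen, and a common SD of 5.414.

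**What to change.** Keep N = 785 and revise Section 7 as follows.

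1. Replace the power of 0.87 with 0.80 for a two-sided 1-df test at effect size 0.1, and describe the 0.2 and 0.3 sizes in the same way. If a one-sided test was intended, declare and justify it, and make power and N agree.
2. Name the test, the effect-size index, the degrees of freedom and the sidedness.
3. State the power of the five-arm comparison at a difference of 3 UTIs with SD 5.414, with the assumed arm sizes and pattern of means, and note that it is only about 0.60 if the effect is 0.1.
4. Give the same figures at the number expected to remain analysable after the 6-month, same-regimen rule, with the loss stated as an assumption. With 20% loss (N = 628) they are 0.71 (1 df) and 0.49 (4 df) at effect 0.1, and about 0.96 or higher for the five-arm ANOVA at a 3-UTI difference.

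The cost is a few sentences and a less favourable stated power at effect 0.1. No extra patients are needed.
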